## Abstract

**Background:**

Internationally, teledermatology has proven to be a viable alternative to conventional physical referrals. Travel cost and referral times are reduced while patient safety is preserved. Especially patients from rural areas benefit from this healthcare innovation. Despite these established facts and positive experiences from EU neighboring countries like the Netherlands or the United Kingdom, Germany has not yet implemented store-and-forward teledermatology in routine care.

**Methods:**

The TeleDerm study will implement and evaluate store-and-forward teledermatology in 50 general practitioner (GP) practices as an alternative to conventional referrals. TeleDerm aims to confirm that the possibility of store-and-forward teledermatology in GP practices is going to lead to a 15% (*n* = 260) reduction in referrals in the intervention arm. The study uses a cluster-randomized controlled trial design. Randomization is planned for the cluster “county”. The main observational unit is the GP practice. Poisson distribution of referrals is assumed. The evaluation of secondary outcomes like acceptance, enablers and barriers uses a mixed-methods design with questionnaires and interviews.

**Discussion:**

Due to the heterogeneity of GP practice organization, patient management software, information technology service providers, GP personal technical affinity and training, we expect several challenges in implementing teledermatology in German GP routine care. Therefore, we plan to recruit 30% more GPs than required by the power calculation. The implementation design and accompanying evaluation is expected to deliver vital insights into the specifics of implementing telemedicine in German routine care.

**Trial registration:**

German Clinical Trials Register, DRKS00012944. Registered prospectively on 31 August 2017.

**Electronic supplementary material:**

The online version of this article (10.1186/s13063-018-2955-2) contains supplementary material, which is available to authorized users.

## Background

Teledermatology is the process of diagnosing dermatologic problems at a physical distance and, in the case of store-and-forward technology, at different times [1]. Internationally, teledermatology is already implemented in a number of healthcare systems [1]. For example, the USA, the Netherlands and the United Kingdom (UK) use teledermatology in clinical routine practice [1–3].

Dermatologic conditions are common in primary care [4–6]. In about 80% of common conditions, the general practitioner (GP) is able to make a diagnosis and initiate treatment based on clinical examination and patient history [7].

If a GP experiences diagnostic uncertainty or if treatment fails, referral to a dermatologist is usually the next step. Physical referrals are often associated with long waiting times for an appointment. Long travel distance between the patient’s home and the dermatologist’s practice is another complication. Thus, teledermatology is a viable alternative to physical referrals—especially in rural areas.

According to previous studies, most common skin diseases can safely be diagnosed by teledermatology [1]. A randomized controlled trial by Whited et al. [8] showed comparable clinical courses and quality of life in 392 patients. The study compared teledermatology with physical referrals to dermatologists. Both patients and care providers evaluated teledermatology positively [8]. Another randomized controlled trial by Eminovic et al. [9] involved 631 patients. The study showed that 21% of all physical referrals to dermatologists could be prevented by teledermatology [9]. Other studies concluded that between 18 and 94% (mean 43%) of physical dermatologist consultations could be prevented by teledermatology [1, 8, 10, 11]. Several studies showed that teledermatology is equal to conventional referrals in terms of accuracy, specificity, sensitivity and clinical endpoints [1, 3, 11–15]. Depending on the health and reimbursement system, teledermatology can lead to cost savings up to 18% compared with conventional referrals [1, 16]. Furthermore, a significant learning effect in GPs was reported. This learning effect is presumed to contribute to a sustainable cost reduction over time [16].

In Germany, however, teledermatology is not yet implemented in routine care. The use of teledermatology in general practice is restricted to local solutions and pilot projects [2, 17]. Specialized first-line dermatologic care in Germany is mainly provided by dermatologists working in their own practices. Only a minority of dermatologists work in hospitals. Thus, access to specialized dermatologic care shows regional differences [18, 19]. Due to the growing number of patients and the relatively difficult access to specialized dermatologic care, GPs will play an increasingly important role in diagnosing and treating dermatologic problems in the future [20]. Demographic change further contributes to the increasing number of skin conditions and malignancies of the skin [4, 20, 21]. Older patients have more difficulties accessing specialized dermatologic care due to reduced mobility [4]. To our knowledge, quite a few patients and GPs in Germany help themselves by using commercial end-to-end encrypted communication platforms such as WhatsApp. Both patients and GPs send clinical data such as dermatologic photographs, radiology images or electrocardiogram (ECG) printouts to specialists to obtain advice. The legality of these actions in the context of rigorous German data protection laws is highly questionable. In summary, this background illustrates the need for telemedicine as an addition to interdisciplinary and cross-sectoral communication in German health care.

Thus, the aim of our study is to evaluate the implementation of teledermatology in primary care in a defined number of counties in Baden-Württemberg, Germany.

## Methods

### Study design and setting

The study is planned as a cluster-randomized controlled confirmatory study, where a county is regarded as one cluster. The main scientific hypothesis is that the possibility of store-and-forward teledermatology in GP practices is going to reduce GP referrals to dermatologists by at least 15%. This protocol follows the Guidance of Standard Protocol Items: Recommendations for Interventional Trials (SPIRIT) 2013 Statement [22]. It includes the schedule of enrolment and relevant assessments (Fig. 1) using the SPIRIT figure template. A SPIRIT checklist is provided in Additional file 1.

**Fig. 1 Fig1:**
[figure not shown]
SPIRIT 2013 figure with schedule of enrolment, interventions and assessments. GP general practitioner, HzV Hausarztzentrierte Versorgung

This project is one of the first to be supported by the Federal Joint Committee’s Innovation Fund. In order to facilitate innovations in German health care, the fund was created in 2015 with the “Law on Strengthening Statutory Health Care” (Gesetzliche Krankenversicherungs-Versorgungsstärkungsgesetz) [23]. The Federal Joint Committee call for proposals is competitive and uses external peer review. The sponsor has no influence over study design; collection, management, analysis and interpretation of data; writing of the report; and the decision to submit the report for publication. Neither does the sponsor have ultimate authority over any of these actions.

To describe the study setting, a short overview of the health insurance system in Germany is presented. There are around 116 statutory health insurance companies in Germany. The Allgemeine Ortskrankenkasse (AOK) is one of the largest statutory health insurance funds with over 25 million insured persons (35% of all statutory insured persons) [24]. Statutory insurance companies are self-governed corporations under public law. The state of Germany or federal regions may be shareholders in these companies. They must provide health services for everyone who is insured. They also must accept every applicant for health services. Private health insurance companies, on the other hand, are basically privately owned.

In addition to their regular coverage, all health insurance companies may sign direct contracts with GP representatives and other specialist physician groups. An example of such a contract is the Hausarztzentrierte Versorgung (HzV) (GP-centered health care). Patients enrolled in the HzV decide to enlist to one GP. Every primary care physician has regular contracts with the Association of Statutory Health Insurance Physicians (KV). This association negotiates outpatient treatment costs with the legislator and the insurance companies. Within the regular contracts, the primary physician is remunerated per consultation and treatment. In the case of GP-centred care, the GP receives an additional amount per capita directly from the insurance company.

The federal state of Baden-Württemberg is one of Germany’s larger states with about 10 million inhabitants. It is organized into several *Landkreise* (counties) with variable population density, ranging from 3008 inhabitants per km^2^ in the urban region of Stuttgart to 101 inhabitants per km^2^ in the rural Main-Tauber County [25]. Likewise, the number of dermatologists per inhabitant varies from one statutory health insurance (SHI) dermatologist per 9617 inhabitants (City of Karlsruhe) to one dermatologist per 130,772 inhabitants (Sigmaringen County) [26]. The SHI GP-to-inhabitant ratio shows less variation: there is between one GP per 1070 inhabitants (Main-Tauber County) and one GP per 1501 inhabitants (Tuttlingen County) [26].

Eight counties were included in the study. Selection criteria for the counties were the closeness to the study center (Tübingen) and their similarity in study-relevant indicators (see Table 1). These parameters will be used for the counties’ matching and randomization process. Allocation of patients to control or intervention groups (−t_2_ in Fig. 1) is based on this randomization.

**Table 1 Tab1:** Matching parameters of the eight study counties in the federal state of Baden-Württemberg

County	Inhabitants per km^2^	Inhabitants	Dermatologist:inhabitant ratio	GP:inhabitant ratio
Böblingen	617	381,281	1:25,419	1:1352
Calw	195	155,359	1:51,786	1:1387
Esslingen	817	524,127	1:29,118	1:1368
Freudenstadt	133	116,233	1:58,117	1:1471
Reutlingen	274	282,113	1:18,808	1:1190
Rottweil	179	137,500	1:27,500	1:1127
Tuttlingen	186	136,606	1:27,321	1:1501
Zollernalbkreis	206	188,595	1:31,433	1:1266

*GP* general practitioner

### Study design

During the first phase of the study (−t_1_ in Fig. 1), GP teams will be recruited in the intervention counties. Further preparations will include the preparation of data protection policies and legal negotiations between insurance companies, middleware providers and GPs. Next, a run-in phase of 6 months will commence. In this phase, the teledermatology system will be implemented in the GP practices and GPs will be trained in the use of the system.

After the run-in phase, 14 months after the beginning of the study, the intervention phase will start. From this point onward, patients can be enrolled (t_0_ in Fig. 1). The phase will last 1 year. Then, a 10-month analysis and publication phase will follow. See Fig. 2 for an overview.

**Fig. 2 Fig2:**
[figure not shown]
Project timeline of the 3-year project. GP general practitioner

The cluster level “county” is randomized into four intervention and four control counties. In the intervention counties, data from non-participating HzV practices will serve as an internal control group at the cluster level “practice”. At the cluster level “patient”, data from nonparticipating patients are used as a second internal control group. No blinding is applied to any level of the trial. Figure 3 shows both study arms and an overview of the different cluster levels.

**Fig. 3 Fig3:**
[figure not shown]
Overview of clusters: different levels or clusters of the project. AOK Allgemeine Ortskrankenkasse, GP general practitioner, HzV Hausarztzentrierte Versorgung

The Institute of General Practice and Interprofessional Care acts as the coordinating center and project lead. In collaboration with the AOK, aQua and the Institute for Clinical Epidemiology and Applied Biometry (IkEaB), the institute also acts as the data management team.

### Outcomes

The primary outcome measure is the number of conventional referrals from GPs to dermatologists.

Secondary endpoints will be evaluated using a mixed-methods approach. This will allow us to evaluate different aspects of the implementation process. For instance, the teledermatology system will provide information about the referral time and process quality. This data source is complemented by questionnaire surveys from all participating groups. Both care providers (GPs, dermatologists, GP practice staff) and patients (teleconsultation patients and patients who have declined a teleconsultations) will receive questionnaires on acceptance and feasibility. Patient questionnaires will also include all items from the Dermatology Life Quality Index (DLQI) [27]. Semi-structured face-to-face interviews (*n* = 15 patients who have received a teledermatology referral and n = 15 care providers, such as GPs, dermatologists and GP practice staff) will provide additional information to the surveys. Lastly, a health economics analysis based on routine data and support costs for the implementation of the teledermatology system is planned. Study sites (GP practices) will be visited once during the intervention phase by a study nurse for audit.

Details about the outcome parameters are presented in Table 2.

**Table 2 Tab2:** Primary and secondary endpoints, data sources and evaluation methods

Secondary endpoints (intervention group)					Primary endpoint (both groups)
Patients	GPs	Dermatologists	GP team staff	Teledermatology software/KSYOS (process evaluation)	Routine data
Care provider/customer satisfaction, description of technical processes with their advantages and disadvantages				• Number of teleconsultations • Time until dermatologist answers • Number of physical referral recommendations • Number of queries by dermatologists after teleconsultation • Type of disease treated by teleconsultation • Duration of complete teleconsultation process • Result of dermatologic consultation	• Number of referrals to dermatologists by GPs • Ambulatory dermatologic diagnoses • Ambulatory patient contacts with GPs and/or dermatologists due to skin conditions (including EBM^a^ keys) • Number of clinic referrals due to skin conditions
• Quality of life (DLQI, questionnaire) • Satisfaction with dermatologic care/telemedicine (questionnaire, interviews)	Appraisal of feasibility, practicability and barriers for implementation (interviews)				
	• Number of reports by dermatologists after consultation (KSYOS and GP PMS) • Time until dermatologist report completed (PMS)	• Recommendation of physical referrals by teledermatologists			

*DLQI* Dermatology Life Quality Index, *EBM* Einheitlicher Bewertungsmaßstab, *GP* general practitioner, *KSYOS* teledermatology system, *PMS* patient management software

^a^Physician’s fee table used to encode what kind of procedure is performed in an outpatient setting and how much money will be paid for it; data are transferred from a practice to the Kassenärztliche Vereinigung and then generate a defined amount of income for the physician

### Intervention (t_1_ in Fig. 1)

The intervention is the provision of all skills and equipment needed to use teledermatology in general practice. If a GP does not feel secure about the management of a dermatologic case, he or she can use teledermatology. Initially, the GP takes standardized pictures of the lesion with a digital camera (Sony Cyber-shot DSC-W810). Next, high-resolution close-up pictures of the lesion are made using a polarized dermatoscope (MEDL4DW DermaScope Polarizer). The GP then creates a teleconsultation. Case-relevant patient data from the patient management system (PMS) are automatically included using middleware. If needed, the GP may provide additional case-relevant information such as the patient’s medical history and a description of symptoms. This information is then pseudonymized and transferred to a server in the Netherlands (KSYOS teledermatology system [3]). Dermatologists with teledermatology training are then notified. If possible, the dermatologists diagnose the lesion and recommend an appropriate course of action. The thus completed report is then sent back to the GP within 48 h. Both the data transfer and authentication use Secure Hypertext Transfer Protocol (https) connections with 256-bit Secure Hash Algorithm (SHA) encryption. An encrypted digital certificate is needed for authentication.

If the information provided by the GP proves insufficient, the dermatologist may either recommend a physical referral to a dermatologist or initiate a “second round”, in which the GP resends the case with possibly better picture quality and more information on the case.

If malignant lesions are found, patients will be referred to specialized dermatologic care. No other restrictions concerning patient care are imposed on the GP teams.

### Recruitment and study flow

The study contains a two-step enrolment process. The first step is to recruit eligible GPs in the intervention counties. Only HzV-contracted GPs will be included. The GPs and their teams will then in turn recruit study participants during the intervention phase (t_0_ in Fig. 1, start 1 July 2018). The patient population of this study comprises all HzV-enrolled, AOK-insured patients in the eight counties. Patients must be at least 18 years of age. Detailed inclusion and exclusion criteria and their role in the recruitment process are shown in Fig. 4.

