**Fig. 4 Fig4:**
[figure not shown]
Recruitment and flow. Flow diagram (adapted and modified from the CONSORT statement) demonstrating how the two-step recruitment process and patient flow work. AOK Allgemeine Ortskrankenkasse, CONSORT Consolidated Standards of Reporting Trials, GP general practitioner, HzV Hausarztzentrierte Versorgung

Study participants are allocated as follows. The family doctors inform eligible patients (see Fig. 4 for criteria) about the study and ask their written consent to participate. After consent has been given and the teledermatology process has been completed, the family doctor enters a value in the patient's PMS entry. This value is visible in the subsequent data analysis and identifies the patient as a study participant. Routine data from the general practitioner's practice PMS are then transmitted to the AOK quarterly via a secure data connection. The AOK aggregates the data for the intervention and control circles.

No written consent is required from patients in the control groups. When patients sign an HzV contract with their insurance company, they consent to the anonymized analysis of their insurance data for scientific and quality management purposes.

Candidates in the intervention group practices who do not meet inclusion criteria (e.g., patients insured by other statutory health insurances or not listed as HzV patients) as well as patients refusing the intervention will be treated as usual and referred to a dermatologist. Eligible patients refusing the interventions will be included in an internal control group (see Fig. 4).

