### Strengths and limitations

The heterogeneity of GP practices, as stated earlier, is one of the major challenges of the study. We expect this to have an impact on the activity of the referring GPs. Therefore, we will recruit 30% more GPs than needed for statistical power to suffice. The internal control group allows us to examine cluster effects.

During the run-in phase of 6 months, first experiences with the technical implementation and the application of the teledermatology system in daily practice are made. This information will allow adjustments of the implementation processes in the GP practices. Also, we aim to address possible data safety concerns on all sides (GPs, patients, AOK). Experiences collected during run-in will be used to constantly inform and improve the ongoing implementation process.

An advantage of this study is that GP participants need little extra training. The intervention is tailored and very close to the reality of routine general practice in Germany. This, with the gained experiences from the study, will help to facilitate a bigger roll-out of teledermatology in German general practice in the future. To enable and plan a large-scale roll-out is a prerequisite for the funding for this study.

Our design allows us to collect information that has an impact from the implementation into routine care such as acceptance among patients and GPs. If the study succeeds, it will be the first teledermatology store-and-forward project to actually pass the barrier from a research project into daily practice, thus reaching new horizons for the much anticipated advance of eHealth in Germany.

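### Practices are recruited after allocation and only in intervention counties, and the stated primary model has no baseline referral rate to offset volunteer differences

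*Protocol article*

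**What the plan says.** **Allocation.** Under Methods, Study design: "The cluster level “county” is randomized into four intervention and four control counties". Study design and setting places this step at −t2: "Allocation of patients to control or intervention groups (−t_2_ in Fig. 1) is based on this randomization". The counties are matched on population density, population size, and dermatologist and GP ratios (Table 1). None of these measures referral behaviour.

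**Recruitment of practices.** This follows at −t1: "GP teams will be recruited in the intervention counties". Recruitment and study flow repeats it: "The first step is to recruit eligible GPs in the intervention counties". The stated restriction is "Only HzV-contracted GPs will be included". No approach to control-county practices is described, and the trial is unblinded at every level.

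**Those who do not take part.** In the intervention counties, "data from non-participating HzV practices will serve as an internal control group" at practice level. At patient level, "Eligible patients refusing the interventions will be included in an internal control group". Strengths and limitations gives the purpose: "The internal control group allows us to examine cluster effects".

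**Primary analysis.** Data analysis specifies a Poisson regression of referrals with the GP as unit, study arm as factor, and KV bills counted over the intervention phase as offset. No earlier referral rate and no other practice characteristic is named.

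**The concern.** Randomising counties makes the counties comparable in expectation. It does not make a volunteering subset of practices in one arm comparable with practices in the other arm that faced no such choice. GPs who agree to take on teledermatology, knowing they will receive it, may differ beforehand in how readily they refer skin problems. They may be more confident in dermatology and refer less, or see more skin disease and refer more.

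The stated model cannot separate such a difference from the intervention effect. The offset accounts for practice size and load, not for a practice's habitual referral rate per bill, and it is measured after the intervention has started. At stake is the causal reading of the single confirmatory test: selection could produce an apparent reduction or conceal a real one.

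**Working it through.** **Inputs from the article (Sample size calculation; Data analysis).** Control mean 48 referrals per practice-year; 15% reduction, so 48 × 0.85 = 40.8 and δ = 7.2; two-sided 5%; 80% power; Poisson counts; t test; 36 practices per arm.

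**Step 1. The plan's own figure.** n per arm = 2(1.96 + 0.842)²σ²/δ².
- σ² = 48 (Poisson, control mean): 2 × 7.849 × 48 / 51.84 = 14.5, so 15.
- σ² = 44.4 (average of 48 and 40.8): 13.4, so 14.

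The stated 36 is not reproduced. Solving for the SD that gives 36: σ = 7.2 / (2.802 × √(2/36)) = 10.9, a variance of 118.9, about 2.5 times Poisson. The article does not state this SD. The mismatch is a separate matter. It is used here only to set two variance scenarios: Poisson, and SD 10.9.

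**Step 2. How a baseline difference enters.** Let r be the ratio of volunteers' to control practices' referral rate per KV bill with no intervention. With study arm and offset only, expected estimated rate ratio = true rate ratio × r.
- True ratio 1.00, r = 0.85: 0.85. The whole target effect appears with no intervention effect.
- True ratio 0.85, r = 0.90: 0.765.
- True ratio 0.85, r = 1.10: 0.935.
- True ratio 0.85, r = 1.15: 0.98. The target effect almost disappears.

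**Step 3. Chance of a significant result when the true effect is zero.** Assumptions: 36 practices per arm, equal KV bills per practice, independent practices, normal approximation. The values of r are assumed, since the article gives none. Write b = 1 − r.
- Poisson: z = −ln(1 − b) / √[1/(36 × 48) + 1/(36 × 48 × (1 − b))].
- SD 10.9: z = 48b / (10.9 × √(2/36)) = 48b / 2.57.
- Rejection probability = Φ(z − 1.96) + Φ(−z − 1.96).

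| Volunteers refer less by | z, Poisson | Rejection | z, SD 10.9 | Rejection |
|---|---|---|---|---|
| 0% | 0 | 5% | 0 | 5% |
| 2.5% | 0.74 | 11.5% | 0.47 | 7.5% |
| 5% | 1.49 | 32% | 0.93 | 15% |
| 10% | 3.01 | 85% | 1.87 | 46% |
| 15% | 4.58 | 99.6% | 2.80 | 80% |

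**Step 4. Dilution in an as-randomised comparison.** Inhabitants divided by inhabitants per GP (Table 1) gives 282, 112, 383, 79, 237, 122, 91 and 149 GPs, in table order. The four smallest counties total 404 and the four largest 1,051. Taking 50 practices at one GP each (an assumption), 50/1,051 = 4.8% and 50/404 = 12.4%. A 15% effect in that share alone would move the all-GP rate by 0.15 × 4.8% = 0.7% to 0.15 × 12.4% = 1.9%. Matching makes both extremes unlikely. The comparison would be restricted to HzV practices, whose number is not given, so the share there would be higher and the dilution smaller.

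**The case against.** Several limits are fair and stand.

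- **Control practices are not shown to be unselected.** A reader might infer this because no recruitment step is described for them. The article does not say how control teams are chosen, the figures with the arms and criteria are not available here, and the control data are themselves limited to HzV patients. What can be said is that no matching volunteering step is described.
- **Refusers and late-flagged patients are not shown to leave the primary count.** The participant flag is set after the teledermatology process is complete, and refusers form an internal control group, so a reader might infer that they are dropped from their practice's total. Nothing says so. The GP is the unit, and the hypothesis concerns having teledermatology available. This needs a clarifying sentence; it is not a demonstrated error.
- **The internal controls have some use.** Non-participating practices can be compared with control counties to look at county differences, and with participants to look at selection. They are nevertheless self-selected and have no stated place in the primary model, so they do not correct it.
- **The size and direction of bias are unknown.** The table in the working is a range under assumption, not a forecast.

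It can also be argued that covariates may be added in an analysis plan not shown here; the article does not say that study arm and offset are the only terms. But it does set out the primary model, and it fixes the order of allocation and recruitment. A baseline term would change the model as published.

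**Conclusion.** The point holds in this form: practices are recruited openly, after county allocation and in one arm only; those that decline are set apart; and the stated primary model contains nothing that adjusts for earlier referral behaviour. County randomisation therefore does not protect the main contrast.

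The sensitivity is substantial. A 5% baseline difference, a third of the target effect, raises the chance of a false significant result from 5% to between 15% and 32%, depending on the variance. A difference in the other direction would mask a real effect. These figures rest on assumed baseline differences and independent practices. The documents do not support a claim that the result will be biased in a particular direction or by a particular amount. The order of recruitment and the terms named in the model are certain; the size of the bias is not.

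**What to change.** In Data analysis, primary outcome:

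1. Add each practice's AOK-HzV dermatology referral rate from a year before the run-in, either as a covariate or through an arm-by-period (difference-in-differences) model.
2. State that every recruited practice, with all its eligible AOK-HzV patients, counts in the intervention arm whether or not teledermatology was used.
3. Add a sensitivity analysis of all HzV practices in the intervention counties against all in the control counties. This keeps the randomised comparison but dilutes the effect, so it supports the primary analysis and does not replace it.
4. Describe both internal control groups as self-selected and descriptive, and word the cluster-effects statement in Strengths and limitations accordingly.

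The cost is one further year of routine data linked by practice, plus wording. That such data are available and can be linked is an assumption; the article does not address it. A rule is needed for practices without a full baseline year. Difference-in-differences requires parallel trends, which volunteers may not satisfy. Neither form of baseline adjustment fully removes the selection bias, and the report should say so.
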